#### ***EX Group***

The EX program is a multi-component intervention based in part on the FAME program^61. We have developed specific guidelines and increments for each exercise in this program to provide safe and objective progression of the participants. Participants will be familiarized with the Borg Rating of Perceived Exertion (RPE) and the scale will be visible in the room. We have previously used the RPE in individuals with chronic stroke and found it representative of myocardial exertion. Each class will have a 10-minute warm-up, three core components—

strength training (20 minutes); aerobic/agility training (20 minutes); and balance training (5 minutes)—and will end with a 5-minute cool down. Strength training will consist of calf raises, squats, bicep curls, tricep extensions, and an alternating fifth activity of either sliding back lunges or standing leg abduction. Exercises will be progressed by adding weight (e.g., dumbbells, completing single calf raise versus double calf raise) or altering movement tempo (e.g., fast concentric motion followed by slow eccentric motion, adding hold at bottom of squat). Aerobic/agility exercises will include heel and toe tapping, low and high knee marches, stepper exercise, agility ladders, and figure 8 walking. Initially, participants will be asked to complete the exercise at an intensity corresponding to a RPE of 12. Exercise intensity will be progressed at a rate of approximately 1 RPE/month, with a final target RPE of 16 during month 6. Balance exercises will have participants complete various movements (e.g., hit balloons, throw ball against wall, walk forward and backward, close eyes, rotate trunk, move arms) while standing and with feet in either side-by-side, semi-tandem, or fully-tandem positions. Heart rate monitors (Polar RS400) will be worn throughout class, with measurement occurring before class, at least twice during class, and at the end of class. The BORG RPE will be administered at least twice during class and at the end of class. Exercise difficulty (e.g., added weight, stepper height) will be recorded during each class, and the Timed-Up-and-Go task and Short Physical Performance Battery will be completed monthly to provide objective performance tracking.

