### *3) General Balance and Mobility*

We will use the Short Physical Performance Battery to assess general mobility and balance. For the Short Physical Performance Battery, participants are assessed on performances of standing balance, walking, and sit-to-stand. Each component is rated out of four points, for a maximum of 12 points; a score < 9/12 predicts subsequent disability. We will also measure knee extension (quadriceps) strength using the method employed by the physiological profile assessment and grip strength (in kg) using a digital Jamar isometric hand dynamometer.

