### ***Cog-Plus Group***

We have designed this program based on the feedback received from our pilot study and based on current evidence. In addition, we aimed to design a program that could feasibly be implemented in the community with minimal resources. Because impairment in multiple cognitive domains is common following stroke, the cognitive exercises included in the program targeted various aspects of cognition, including learning and memory, processing speed, attention, working memory, and executive functions. Each class will begin with the participants being asked to memorize a 7-item word list. Next, each participant will complete approximately 15 minutes of the brain training program Lumosity using an individually-issued Apple iPad. Lumosity consists of various short games (typically 1 to 5 minutes) that target various aspects of cognition (e.g., working memory, divided attention, processing speed). Each class, participants will be encouraged to complete at least 5 distinct games. For the remaining class time (approximately 30 minutes), the participants will complete a variety of social games and mental activities in pairs or as entire class. Some of these activities will utilize apps on the Apple iPads (e.g., *Heads-Up*, *Teledoodle*), and others are based on improvisation and mental activities from the PERK program^64. At the end of class, participants will recall as many of the words from the word list; they will use the Notes program on the iPad to record the recalled words. Approximately every month, the class instructor will meet individually with the participants to show performance progress on the Lumosity training program and to discuss outstanding concerns and areas of improvement (e.g., short-term memory, speed of responding). Every month, the 7-item word list will be replaced with a 15-item word list, and participants will be requested to recall those words immediately, as well as at the end of the class.

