### ***CON Group***

The CON program will follow the protocol used in [name] previous RCT. The CON protocol will consist of stretches, deep breathing and relaxation techniques, general posture education, general core control exercises, grip strength and dexterity exercises, and light

isometric toning exercises. Some exercises from the EX program will also be included but in a simplified format without progression (e.g., double calf raises, heel and toe tapping, balance exercises). Once a month, the class will consist of educational lecture and will include topics such as sleep hygiene, goal setting, and nutrition. This group will serve to control for confounding variables such as physical training received by traveling to the community centre for twice-weekly classes and changes in lifestyle secondary to study participation. The Timed-Up-and-Go task will be completed on a monthly basis to allow for objective physical performance tracking.

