### ***Secondary & Tertiary Outcomes***

Analyses will be descriptive; no alpha has been allocated. Point and interval estimates for the effect of the intervention on each of the secondary outcomes at six and 12 months will be determined separately using linear mixed models. Multiple linear regression analyses will also be performed to explore the association between change in cognitive function, after accounting for experimental group, baseline age, baseline global cognition, and: 1) superior treatment adherence; 2) change in physical activity levels outside the research protocol; and 3) change in general balance and mobility. Randomization integrity will be determined by examining bias in the blocking sequence used to produce allocation sequence.

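### The Short Physical Performance Battery is a secondary outcome, yet only the EX arm also takes it monthly in class, so its EX contrasts may include a practice effect

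*Protocol*

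**What the plan says.** Under Secondary Outcome Measures, General Balance and Mobility, the protocol states "We will use the Short Physical Performance Battery" and describes a score out of 12: "For the Short Physical Performance Battery, participants are assessed on performances of standing balance, walking, and sit-to-stand". The Measurement section sets three main sessions: baseline, 6 months and 12 months. The Secondary & Tertiary Outcomes section plans point and interval estimates at 6 and 12 months from linear mixed models, with no alpha allocated. It also names "change in general balance and mobility" as an explanatory variable for cognitive change, in a regression that accounts for experimental group.

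The Interventions section describes in-class tracking separately for each arm:

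- EX Group: "the Timed-Up-and-Go task and Short Physical Performance Battery will be completed monthly to provide objective performance tracking".
- CON Group: the Timed-Up-and-Go "will be completed on a monthly basis to allow for objective physical performance tracking". The SPPB is not mentioned.
- Cog-Plus Group: "Approximately every month, the class instructor will meet individually with the participants to show performance progress on the Lumosity training program". No physical test is described.

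The CON Group section also includes grip and dexterity exercises and a monthly lecture that "will include topics such as sleep hygiene, goal setting, and nutrition". Grip strength and actigraphic sleep quality are both secondary outcomes.

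**The concern.** The SPPB is a scored performance test. A participant who has repeated it several times may do better because the tasks, instructions and timing are familiar. If one arm rehearses the test and the others do not, that gain enters the between-arm difference, and the outcome data cannot separate it from a true gain in mobility. The difference lies in the participant, so the blinded assessor described in the Design Outline does not remove it.

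The in-class SPPB is there for tracking and is not one of the EX training components. A practice gain from it is therefore a measurement artefact and not part of the exercise effect. At stake are the SPPB point and interval estimates for EX versus CON and EX versus Cog-Plus, in a proof-of-concept trial whose results are meant to inform a larger one.

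**Working it through.** The protocol gives no practice effect and no SD for the SPPB, so there is no stated figure to reproduce. The check is a comparison of sections, followed by a calculation of scale under assumptions.

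**1. Is the SPPB monthly in all arms?** The Measurement section says that further secondary measures are taken monthly. The section on monthly secondary measures names only two: the CHAMPS physical activity questionnaire and the Nottingham Leisure Questionnaire. The SPPB is not among them, so the monthly SPPB belongs to the EX classes alone.

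**2. Exposure between baseline and month 6.** Classes run for 26 weeks, about six months. Monthly testing gives 5 or 6 in-class administrations, depending on whether the last one coincides with the 6-month assessment.

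| Arm | In-class SPPB | In-class Timed-Up-and-Go |
|---|---|---|
| EX | about 5-6 | monthly |
| CON | 0 | monthly |
| Cog-Plus | none described | none described |

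The asymmetry affects EX-CON and EX-Cog-Plus. It does not affect Cog-Plus versus CON.

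**3. Scale for EX-CON.** The Sample Size Calculation gives 34 participants in EX and 52 in the control arm (called BAT there). For an unadjusted difference in SD units:

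SE = sqrt(1/34 + 1/52) = sqrt(0.02941 + 0.01923) = 0.221.

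With the protocol's 15% attrition, the numbers become 34 × 0.85 = 28.9 and 52 × 0.85 = 44.2, and SE = sqrt(1/28.9 + 1/44.2) = 0.239.

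If practice shifts the EX mean by b SD, a nominal 95% interval covers the true difference with probability Φ(1.96 − b/SE) − Φ(−1.96 − b/SE). For b = 0.2 and SE = 0.221, b/SE is about 0.907, and Φ(1.053) − Φ(−2.867) = 0.852.

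| Assumed shift b (SD) | Coverage, 34 vs 52 | Coverage, 28.9 vs 44.2 |
|---|---|---|
| 0.05 | 94.4% | 94.5% |
| 0.1 | 92.6% | 93.0% |
| 0.2 | 85.2% | 86.7% |
| 0.3 | 72.5% | 75.9% |
| 0.5 | 37.9% | 44.8% |

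The shifts are assumptions; nothing in the protocol selects a row.

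**4. The regression of cognitive change.** Write the model as ΔCog = a + g(arm) + c × ΔSPPB. If every EX participant gains the same practice amount δ, the observed ΔSPPB in EX is the true change plus δ. The EX group term then falls by c × δ, and c is unchanged. Because the protocol accounts for experimental group, a uniform shift is absorbed. Only person-to-person variation in practice gain within EX would remain, for example through differing class attendance, and the protocol gives nothing from which to size it.

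**The case against.** The strongest objection is that EX trains similar tasks anyway. Two classes a week for 26 weeks make 52 classes with squats, walking drills and balance work in the same kinds of stance. Five or six tracking tests look small beside that, and most task familiarity would stay if they were dropped. The secondary analyses are also descriptive, the trial is proof-of-concept, and the ADAS-Cog-Plus is not touched.

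Much of this stands. It rules out saying that the SPPB contrasts are biased by a known or large amount. But familiarity gained through training is part of the intervention, whereas repeating the scored test for tracking is not and can be avoided. The lack of an alpha is no protection either: the planned output is point and interval estimates, and a one-directional shift affects exactly those.

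A reader might go further and infer that the CON programme biases other outcomes, since only CON has named grip exercises and sleep-hygiene or nutrition lectures, while the outcomes include "grip strength (in kg) using a digital Jamar isometric hand dynamometer", sleep quality and blood markers. The protocol does not support that. CON is a declared active control, and this content is part of the randomised comparator, so the contrasts are valid against this programme. The lecture topics are examples for one class a month, the blood draw is optional, and EX also does arm exercises progressed with dumbbells. The consequence is one of interpretation: these results compare each programme with an active control and not with an inert one.

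**Conclusion.** The point holds as a limited measurement concern. EX alone takes a secondary outcome test about 5 to 6 extra times before month 6, so the EX-CON and EX-Cog-Plus SPPB estimates may include a practice effect favouring EX that assessor blinding does not remove. Its size cannot be derived from the protocol: over the assumed range of 0.05 to 0.5 SD it runs from negligible to serious. That range rests on an unadjusted comparison at the stated arm sizes and a practice gain shared across EX. The protocol also says nothing about whether such a gain would last to month 12, six months after classes end.

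Cog-Plus versus CON, the primary outcome and the sample size are unaffected. It would be tempting to conclude that the mobility-cognition regression inherits the error, but the group term absorbs a uniform shift.

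**What to change.** Remove the SPPB from the monthly tracking in the EX Group section and keep the Timed-Up-and-Go, which is not a listed outcome and is already used for the same purpose in EX and CON. State in General Balance and Mobility that all arms take the SPPB only at baseline, 6 months and 12 months. The cost is one fewer in-class tracking measure in EX, where exercise load, heart rate, perceived exertion and the Timed-Up-and-Go remain.

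If EX classes have already been delivered with the monthly SPPB, report the extra administrations beside the EX contrasts as a possible source of practice gain.

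The CON programme needs no design change. Describe the grip and sleep contrasts as comparisons with this active programme.

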### ***Cog-Plus Group***

We have designed this program based on the feedback received from our pilot study and based on current evidence. In addition, we aimed to design a program that could feasibly be implemented in the community with minimal resources. Because impairment in multiple cognitive domains is common following stroke, the cognitive exercises included in the program targeted various aspects of cognition, including learning and memory, processing speed, attention, working memory, and executive functions. Each class will begin with the participants being asked to memorize a 7-item word list. Next, each participant will complete approximately 15 minutes of the brain training program Lumosity using an individually-issued Apple iPad. Lumosity consists of various short games (typically 1 to 5 minutes) that target various aspects of cognition (e.g., working memory, divided attention, processing speed). Each class, participants will be encouraged to complete at least 5 distinct games. For the remaining class time (approximately 30 minutes), the participants will complete a variety of social games and mental activities in pairs or as entire class. Some of these activities will utilize apps on the Apple iPads (e.g., *Heads-Up*, *Teledoodle*), and others are based on improvisation and mental activities from the PERK program^64. At the end of class, participants will recall as many of the words from the word list; they will use the Notes program on the iPad to record the recalled words. Approximately every month, the class instructor will meet individually with the participants to show performance progress on the Lumosity training program and to discuss outstanding concerns and areas of improvement (e.g., short-term memory, speed of responding). Every month, the 7-item word list will be replaced with a 15-item word list, and participants will be requested to recall those words immediately, as well as at the end of the class.

### ***CON Group***

The CON program will follow the protocol used in [name] previous RCT. The CON protocol will consist of stretches, deep breathing and relaxation techniques, general posture education, general core control exercises, grip strength and dexterity exercises, and light

isometric toning exercises. Some exercises from the EX program will also be included but in a simplified format without progression (e.g., double calf raises, heel and toe tapping, balance exercises). Once a month, the class will consist of educational lecture and will include topics such as sleep hygiene, goal setting, and nutrition. This group will serve to control for confounding variables such as physical training received by traveling to the community centre for twice-weekly classes and changes in lifestyle secondary to study participation. The Timed-Up-and-Go task will be completed on a monthly basis to allow for objective physical performance tracking.

### **Data and Adverse Events Monitoring**

A Data and Safety Monitoring Committee will be established by co-investigators who will be independent from the day-to-day conduct of the study and from the study funders. Drs. [name], [name], [name], and [name] will review all adverse events reported in the study on a monthly basis. They will stop the study if the adverse events data demonstrate any hazards that are the result of the intervention. They will also ensure data sharing and fidelity. Data provided to project team members will exclude identifying participant information.

### **Strategies to Promote Adherence**

We will implement strategies to promote adherence during the 6-month intervention as recommended by the literature. These will include: 1) monthly phone calls by the unblinded research coordinators to encourage adherence to classes; multiple contacts have been shown to be more effective than single exposures; 2) discussing participant barriers and developing coping plans and action plans; 3) setting implementation intentions and concrete plans; and 4) encourage participants to continually self-monitor their progress with monthly calendars provided by the study. This strategy has been identified as the most successful behavioural/cognitive approach when compared to all other current adherence techniques.

### **Sample Size Calculation**

We have designed our trial to allow the evaluation of statistical significance of the treatment effect between groups on the ADAS-Cog-Plus. A number of pharmaceutical RCTs in vascular dementia – a population highly relevant to our proposed study – have shown positive cognitive effects as measured by the ADAS-Cog, and it has been suggested that the ADAS-Cog-Plus shows greater sensitivity to underlying changes in cognition. A previous RCT of physical activity in older adults at risk for Alzheimer's disease with ADAS-Cog as the primary outcome measure demonstrated a standardized effect size of 0.60^17. We used interim results from our PROMOTE study – an exercise RCT in adults with mild sub-cortical ischaemic vascular cognitive impairment – for our sample size estimation. Based on data collected from 15 participants who have completed the RCT, we found the mean change in the ADAS-Cog score was 2.7 (SD=2.3) and 0.87 (SD=3.4) for the exercise training group and the control group, respectively. The minimally clinically relevant change (MCRC) on the ADAS-Cog varies between 3 and 5 points, with a change of  $\geq 4$  being recommended by the Food and Drug Administration. Recently, Schrag and colleagues established the MCRC empirically using data collected from the Alzheimer's disease Neuroimaging Initiative. They found that a 3-point change on the ADAS-Cog is an appropriate MCRC. Assuming a mean change of 3 points on the ADAS-Cog for both the EX and Cog-Plus groups and a mean change of 1 point for the CON group at 6 months, a common standard deviation of 2.85, and an alpha of 0.05, 39

participants per group (i.e., total sample of 117) will provide a power greater than 0.80^79. We then assumed a standardized effect size of 0.7 for the ADAS-Cog-Plus, as it has greater sensitivity to changes in cognitive function compared with the 11- or 13-item ADAS-Cog. After accounting for 15% attrition and 2:2:3 allocation, 34 participants were randomized to the EX group, 34 to the ENRICH group, and 52 to the BAT group, for a total sample of 120.

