## **Statistical Analyses**

### ***Primary Outcome***

This analysis will follow the intention-to-treat principal, such that all randomized participants will be included to estimate treatment effects, irrespective of deviations from treatment protocol (e.g., loss to follow-up, non-compliance). This will be done using linear mixed models using maximum likelihood estimation. The model will include random intercepts and slopes, and fixed effects of time (baseline, month 6, month 12), treatment assignment (CON, EX, Cog-Plus), and their interaction. Baseline MMSE and ADAS-Cog-Plus scores will also be included as fixed effect covariates. Time will be specified as a categorical variable, thus allowing us to examine treatment differences at the primary endpoint (month 6) and then, as a secondary objective, whether those differences persist at the 6-month follow-up (month 12). Two planned simple contrasts will be performed using the Dunnett test. These contrasts will be employed to assess differences between: 1) the EX group and the CON group; and 2) the Cog-Plus group and the CON group. The overall alpha will be set at 0.05. A secondary complete-case analysis will be conducted using this linear mixed model, in which participants with valid data at all time points will be included. As an exploratory strategy, multiple imputation will be used to judge the impact of missingness on the conclusions drawn from this study.

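### The total of 120 matches an unadjusted comparison, while the primary analysis uses Dunnett contrasts, for which power after 15% loss is about 0.75 unless credit is taken for baseline adjustment

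*Protocol*

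**What the plan says.** The Sample Size Calculation section of the protocol builds the number in three steps.

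1. Inputs on the ADAS-Cog: "Assuming a mean change of 3 points on the ADAS-Cog for both the EX and Cog-Plus groups", "a mean change of 1 point for the CON group at 6 months", "a common standard deviation of 2.85, and an alpha of 0.05". From these, 39 "participants per group (i.e., total sample of 117) will provide a power greater than 0.80". The section names no test, sidedness or multiplicity adjustment. It does not say whether 39 counts evaluable or randomised participants.
2. Change of scale: "We then assumed a standardized effect size of 0.7 for the ADAS-Cog-Plus, as it has greater sensitivity to changes in cognitive function".
3. Final numbers: "After accounting for 15% attrition and 2:2:3 allocation, 34 participants were randomized to the EX group, 34 to the ENRICH group, and 52" to the third arm, 120 in all. No power figure is attached to this total.

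The Primary Outcome section under Statistical Analyses fixes the test: "Two planned simple contrasts will be performed using the Dunnett test". The contrasts are EX against CON and Cog-Plus against CON, with an overall alpha of 0.05. The model is a linear mixed model on all randomised participants, with baseline MMSE and ADAS-Cog-Plus as covariates.

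**The concern.** A reader takes the power above 0.80 from the first step and applies it to the 120 participants in the last. The two are linked only by a sensitivity argument, and that argument does not change the effect size. The analysis section then spends the 5% alpha across two contrasts, an adjustment that the sizing does not mention.

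At stake is how a non-significant contrast is read. The section says that the trial was designed to test the treatment effect for significance, and the Introduction says that the results will inform a larger definitive trial. If the power for the planned test is nearer 0.75 than above 0.80, the protocol should say so, or should say what makes up the difference.

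**Working it through.** **Inputs.** From the Sample Size Calculation: mean changes 3 and 1, SD 2.85, alpha 0.05, attrition 15%, allocation 2:2:3, randomised 34/34/52. From the Primary Outcome section: two Dunnett contrasts with CON, overall alpha 0.05. Assumed: two-sided testing, attrition complete by month 6, participants lost contribute nothing, no credit for covariates. The last two arms of the sizing, labelled ENRICH and BAT, are read as Cog-Plus and CON from the allocation ratio.

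**Effect size.** d = (3 - 1)/2.85 = 0.702. The value then assumed for the ADAS-Cog-Plus is 0.7, so no gain in sensitivity enters.

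**Where 39 per group can come from.** Two routes reproduce it.
- *Dunnett, 39 evaluable per group.* The two-sided critical value is 2.24 (114 df) and per-contrast power at d = 0.702 is 0.804. At 38 per group it is 0.792, so 39 is the smallest number above 0.80.
- *Unadjusted t-test, attrition included.* 33 per group give power 0.802 at d = 0.702, and 33/0.85 = 38.8, rounded up to 39.

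**Where 120 comes from.** At d = 0.7 the unadjusted two-sided t-test needs 34 per group (33 give 0.7997, 34 give 0.812). Then 3 x 34 = 102 and 102/0.85 = 120. Split 2:2:3: 120 x 2/7 = 34.3 and 120 x 3/7 = 51.4, stated as 34/34/52. The final total therefore matches an unadjusted comparison exactly.

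**Power of the 120 under the planned test.** Evaluable: 34 x 0.85 = 28.9, again 28.9, and 52 x 0.85 = 44.2; total 102, pooled df 102 - 3 = 99.
- Noncentrality = d x sqrt(n1 x n0/(n1 + n0)) = 0.70 x sqrt(28.9 x 44.2/73.1) = 0.70 x sqrt(17.47) = 2.93.
- Dunnett two-sided critical value: about 2.25 (correlation between contrasts 28.9/73.1 = 0.395).
- Power from the noncentral t distribution:

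| Condition (d = 0.70) | Power |
|---|---|
| Dunnett, 28.9/28.9/44.2, per contrast | 0.75 |
| Same, at least one contrast | 0.89 |
| Same, both contrasts | 0.61 |
| Unadjusted 0.05, 28.9/28.9/44.2 | 0.83 |
| Dunnett, 34/34/52, no attrition | 0.82 |

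The effect detectable with 80% power per Dunnett contrast is 0.74 SD, or 0.74 x 2.85 = 2.1 ADAS-Cog points. Power of 0.80 at d = 0.70 and 2:2:3 needs about 115 evaluable, or about 136 randomised.

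**Either reading of 39 after 15% loss, under Dunnett.** If 39 is evaluable, 117/0.85 = 137.6, so 138 would have to be randomised, not 120. If 39 already includes attrition, 33 per group remain and Dunnett power is about 0.73.

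**Effect of the planned baseline covariate.** The protocol gives no baseline to month-6 correlation (rho), so these values are assumptions. With equal variances, the change-score variance is 2 x sigma^2 x (1 - rho) and the baseline-adjusted variance is sigma^2 x (1 - rho^2). The SD ratio is sqrt((1 + rho)/2), and the effective d is 0.70 divided by that ratio.

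| rho | SD ratio | Effective d | Dunnett power, 102 evaluable |
|---|---|---|---|
| 0.5 | 0.866 | 0.81 | 0.87 |
| 0.7 | 0.922 | 0.76 | 0.82 |
| 0.78 | 0.943 | 0.74 | 0.80 |
| 0.9 | 0.975 | 0.72 | 0.77 |

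**The case against.** The strongest reply has four parts.

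- *The sentence on power is true.* It concerns 39 per group, and at 39 evaluable per group both tests reach 0.80 (Dunnett 0.80, unadjusted about 0.86). This stands. The defect is that no power is given for the 120 actually randomised under the planned test, so the reader carries the figure over.
- *The total may contain no arithmetic slip.* A reader might infer that 39 is the evaluable number for the Dunnett test, so that the total ought to have been 138. The document does not support that: it names no test, and the unadjusted route explains both 39 and 120 with attrition already counted. On that reading, inflating 117 again would count attrition twice. But that reading confirms that the sizing omits the adjustment the analysis imposes.
- *The planned model adjusts for baseline.* A reader might infer that the primary analysis is certainly below 0.80. That does not follow either: with equal variances, a correlation of about 0.78 or lower restores it. The protocol neither states a correlation nor claims this credit, so its text cannot settle the matter.
- *Attrition by month 6 may be below 15%.* The section does not say whether the 15% applies to month 6 or to month 12. At 5%, 7.5% and 10% loss, Dunnett power without covariate credit is 0.80, 0.79 and 0.77. This narrows the gap.

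The trial also calls itself proof-of-concept, which limits the consequence. It does not remove the inconsistency, because the sizing is expressly for significance testing.

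**Conclusion.** The point holds as a mismatch between the sizing and the planned test. On the protocol's own inputs (d = 0.70 on the change-score SD, 15% lost, 34/34/52 randomised), power per Dunnett contrast is about 0.75. It passes 0.80 only if the Dunnett adjustment is dropped, if attrition is ignored or is no more than about 5% by month 6, or if credit is taken for baseline adjustment. Neither reading of 39 per group delivers 0.80 under Dunnett after 15% loss without that credit, and the sensitivity argument offsets nothing.

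The result rests on two-sided testing, all attrition falling by month 6 and no information from those lost. The shortfall is moderate, about five percentage points below 0.80, and is a matter of correct statement rather than a flaw in the design.

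**What to change.** Keep 120 and revise the Sample Size Calculation section:

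- Name the test (two-sided Dunnett, two contrasts with CON, overall alpha 0.05), and say whether 39 per group is evaluable or already inflated.
- Give the evaluable numbers and their power. For example: with 34/34/52 randomised and 15% lost by month 6, about 102 evaluable participants (29/29/44) give about 75% power per Dunnett contrast for a standardised effect of 0.70, or 80% for 0.74.
- Say at which visit the 15% applies.
- Delete the justification by greater sensitivity, since 0.7 is the value already used for the ADAS-Cog.
- If credit is taken for the baseline ADAS-Cog-Plus covariate, state the assumed correlation and show the power over a range such as 0.5 to 0.9.

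The cost is a text change and a slightly less favourable stated power. The sample size, allocation and analysis stay as they are.
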